| 
Safety endpoints
 | 
Secondary efficacy endpoints :
 
 
• All cause Death at day 40 and Overall Survival
 
• WHO-COVID-19 Scale
 
• NEWS-2 Scale
 
• Respiratory Rate status defined as:: 
 
○ Normal: < 20/min,
 
○ Mild: <math>20/\text{min} \leq \text{RR} < 24/\text{min}</math>,
 
○ Moderate: <math>24/\text{min} \leq \text{RR} < 30/\text{min}</math>,
 
○ Severe: <math>\geq 30/\text{min}</math>,
 
○ Death.
 
 
 
• Hypoxemia status defined as:: 
 
○ Normal: > 300 mmHg,
 
○ Mild: <math>200 \text{ mmHg} < \text{PaO}_2/\text{FiO}_2 \leq 300 \text{ mmHg}</math>,
 
○ Moderate: <math>100 \text{ mmHg} < \text{PaO}_2/\text{FIO}_2 \leq 200 \text{ mmHg}</math>,
 
○ Severe: <math>\text{PaO}_2/\text{FIO}_2 \leq 100 \text{ mmHg}</math>,
 
○ Death.
 
 
 
• SpO2 status defined as: 
 
○ Normal: > 95%
 
○ Mild: <math>93\% < \text{SpO}_2 \leq 95\%</math>,
 
○ Moderate: <math>90\% < \text{SpO}_2 \leq 93\%</math>,
 
○ Severe: <math>\leq 90\%</math>,
 
○ Death.
 
 
 
• Chest CT-Scan (or in exceptional cases, chest radiogram)
 
• Oxygen-free days (over the study period = 40 days),
 
• Need for mechanical ventilation,
 
• Mechanical ventilation-free days,
 
• Hospital-free days (over study period = 40 days),
 
• Clinical recovery and Time to Clinical recovery (over study period = 40 days),
 
• Cure and Time-to-cure (over study period = 40 days).
 

 
• Incidence, nature and severity of Adverse Events, SAEs, SUSARs and Treatment-Emergent Adverse Events (TEAEs),
 
• Incidence of bleeding-related events,
 
• Incidence of hypersensitivity reactions,
 
• Changes to vital signs over the course of the study versus screening,
 
 |

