|  | 
As this is an estimation study, no adjustment for multiplicity will be proposed.
 
Methods for handling missing data will be further detailed in the SAP.
 
Analysis Sets:
 

• Safety set: All enrolled patients having received at least one dose of the prescription of study medication (either ACT017 or placebo). The Safety set will be the basis for safety analyses. Patients will be assigned to the treatment group as treated for the Safety set.

• All Randomized Set (ITT set): All patients who are randomized into the study and considered as randomized, i.e. with study drug assignments designated according to initial randomization, regardless of whether subjects received what was assigned. Sensitivity efficacy analyses conducted on ITT set could be considered.

• Full Analysis Set (FAS): All randomized patients having received at least one dose of the prescription of study drug (either glenzocimab or placebo). Patients will be assigned to the treatment group as randomized (i.e. with study drug assignments designated according to initial randomization, regardless of whether subjects received what was assigned). The FAS will be considered as the primary set for efficacy analyses.

• Per protocol (PP) set: All FAS patients without any major protocol deviation. Major protocol deviations will be identified during data blind review meetings (i.e.) held before unblinding and database lock.

 
Efficacy Analyses
 
Primary efficacy endpoint: Progression from moderate to severe respiratory distress assessed at Day 4
 
Progression from moderate to severe respiratory distress assessed at Day 4 is a composite failure endpoint defined as the occurrence of at least one of the following failure events :
 

- RR <math>\geq</math> 30/min, or

- SpO2 decrease > 5% in ambient air. In case where oxygenotherapy cannot be discontinued, please refer to

 |

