|  | 
NEWS 2 Scale (item SpO2, scale 2) for adequate conversion (e.g. 93-94 on O2 corresponding to 86-87 in ambient air), PaO2/FiO2 <math>\leq</math> 100mmHg,
 
 
- Death occurring prior to or on Day 4
 
 
The composite event rate will be estimated within each group. The difference in composite event rates and the odds ratio will be estimated along with their asymptotic and exact 95% confidence intervals. p-values from the chi-square and exact Fisher test will also be provided.
 
Methods for handling missing components will be detailed in the SAP.
 
A component-wise secondary analysis will also be provided. No adjustment for multiplicity will be used.
 
An additional multi-component analysis will be performed to assess the proportion of patients with one failure only, 2 failures and 3 failures among the 3 components (except death).
 
Sensitivity analyses will be proposed and detailed in the SAP.
 
Additional analyses of the primary endpoint: the primary composite endpoint will be analyzed in a logistic regression model including treatment effect and relevant covariates ( e.g. baseline WHO-Covid-19 scale) that will be specified in the SAP.
 
Subgroup analyses:
If feasible (i.e. when subgroup sizes are sufficient), subgroup analyses of the primary endpoint will be performed by BMI (<30 vs <math>\geq</math>30), Age (<65 vs <math>\geq</math>65 years), by baseline WHO-Covid-19 scale, comorbidity, concomitant medications will be provided and further detailed in the SAP.
 
The same analysis proposed for the primary efficacy endpoint assessed at day 4 will be provided at other time points (Days 1, 2, 3, 7, 14, 20, and 40). The primary endpoint and its components will also be described via plots (e.g., stacked bar plots representing the proportion of subjects in each category (failure or not) , by treatment arm, over time).
 
Secondary efficacy endpoints
 
 
○ All-Cause Mortality at day 40 (ACM40)
 
 |

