## 8. PRIMARY ENDPOINT

### 8.1 EFFICACY

#### 8.1.1 Primary Efficacy Endpoint : Progression from moderate to severe respiratory distress assessed at Day 4

The primary efficacy endpoint is a composite failure endpoint defined as the occurrence of at least one of the following failure events at Day 4 :

- $RR \geq 30/\text{min}$ , or/and
- $SpO_2$  decrease  $> 5\%$  in ambient air. In case where oxygenotherapy cannot be discontinued, please refer to NEWS 2 Scale (item  $SpO_2$ , scale 2) for adequate conversion (e.g. 93-94 on  $O_2$  corresponding to 86-87 in ambient air),  $PaO_2/FiO_2 \leq 100\text{mmHg}$  or/and
- Death occurring prior to or on Day 4

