## 18. APPENDICES

### Appendix 1: NEWS-2 Scale

| National Early Warning Score (NEWS)* |       |          |             |             |             |           |            |
|--------------------------------------|-------|----------|-------------|-------------|-------------|-----------|------------|
| PHYSIOLOGICAL PARAMETERS             | 3     | 2        | 1           | 0           | 1           | 2         | 3          |
| Respiration Rate                     | ≤8    |          | 9 - 11      | 12 - 20     |             | 21 - 24   | ≥25        |
| Oxygen Saturations                   | ≤91   | 92 - 93  | 94 - 95     | ≥96         |             |           |            |
| Any Supplemental Oxygen              |       | Yes      |             | No          |             |           |            |
| Temperature                          | ≤35.0 |          | 35.1 - 36.0 | 36.1 - 38.0 | 38.1 - 39.0 | ≥39.1     |            |
| Systolic BP                          | ≤90   | 91 - 100 | 101 - 110   | 111 - 219   |             |           | ≥220       |
| Heart Rate                           | ≤40   |          | 41 - 50     | 51 - 90     | 91 - 110    | 111 - 130 | ≥131       |
| Level of Consciousness               |       |          |             | A           |             |           | V, P, or U |

*Appendix 2: WHO COVID-19 Ordinal Scoring Scale*

| Patient State                          | Descriptor                                            | Score |
|-----------------------------------------------|--------------------------------------------------------------|--------------|
| Uninfected                      | No clinical or virological evidence of infection             | 0            |
| Ambulatory                      | No limitation of activities                                  | 1            |
|                                               | Limitation of activities                                     | 2            |
| Hospitalized
Mild disease   | Hospitalized, no oxygen therapy                              | 3            |
|                                               | Oxygen by mask or nasal prongs                               | 4            |
| Hospitalized
Severe Disease | Non-invasive ventilation or high-flow oxygen                 | 5            |

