**2 Estimating FiO2**

| Method                   | O 2 flow (l/min) | Estimated FiO 2 (%) |
|--------------------------|-----------------------------|--------------------------------|
| Nasal cannula            | 1                           | 24                             |
|                          | 2                           | 28                             |
|                          | 3                           | 32                             |
|                          | 4                           | 36                             |
|                          | 5                           | 40                             |
|                          | 6                           | 44                             |
| Nasopharyngeal catheter  | 4                           | 40                             |
|                          | 5                           | 50                             |
|                          | 6                           | 60                             |
| Face mask                | 5                           | 40                             |
|                          | 6-7                         | 50                             |
|                          | 7-8                         | 60                             |
| Face mask with reservoir | 6                           | 60                             |
|                          | 7                           | 70                             |
|                          | 8                           | 80                             |
|                          | 9                           | 90                             |
|                          | 10                          | 95                             |

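### The SpO2 part of the primary endpoint relies, for patients on oxygen, on a conversion that Appendix 1 does not print and whose only example ignores oxygen flow, so it can misclassify in both directions

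*Protocol*

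**What the plan says.** The primary endpoint is progression from moderate to severe respiratory distress at Day 4. It is a composite of respiratory rate of 30/min or more, an SpO2 criterion, PaO2/FiO2 of 100 mmHg or less, and death. The SpO2 criterion is "SpO2 decrease > 5% in ambient air". Section 8.1.1 adds: "In case where oxygenotherapy cannot be discontinued, please refer to NEWS 2 Scale". The Synopsis (Statistical Methods, primary efficacy endpoint) gives the reference and its only example as "NEWS 2 Scale (item SpO2, scale 2) for adequate conversion (e.g. 93-94 on O2 corresponding to 86-87 in ambient air". The same rule stands in the Synopsis under Efficacy Endpoints and in Section 11.5.1. Inclusion criterion 5 (Section 5.1.1) uses the same conversion at entry.

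Two appendices bear on this:

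- **Appendix 1** is headed NEWS-2, but its table has a single saturation row, "Oxygen Saturations", with bands ≤91, 92-93, 94-95 and ≥96, and a yes/no row for supplemental oxygen.
- **Appendix 3** converts SpO2 to PaO2 and converts device and flow to FiO2, from 24% on a nasal cannula at 1 L/min to 95% on a "Face mask with reservoir" at 10 L/min. Section 5.1.1 and the baseline visit (Section 7.3) cite it for PaO2/FiO2. No passage cites it for SpO2.

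Section 11.5.1 lists PaO2/FiO2 ≤100 as its own component and counts three components besides death. Section 8.1.1 and the Synopsis statistical text run it into the SpO2 bullet.

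**The concern.** A patient on oxygen is compared with a reading taken, or imputed, in ambient air. The comparison is meaningful only if the conversion is defined for every reading and reflects how much oxygen is being given. Here the cited scale is not in the protocol, so readings other than 93-94 cannot be converted from it. The one pair that is given yields the same ambient-air value at any flow.

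A single failed component fails the composite, so an SpO2 error passes directly into the primary result. Errors that do not depend on arm would pull the estimated difference towards zero. That matters in a study whose stated aim is to estimate the treatment difference for later trials. Different centres could also improvise different conversions.

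**Working it through.** **Inputs.** From Appendix 3: SpO2 86, 87, 93 and 94% correspond to PaO2 52, 53, 69 and 73 mmHg. FiO2 is 0.24, 0.28 and 0.32 on a nasal cannula at 1, 2 and 3 L/min, 0.60 on a face mask at 7-8 L/min, and 0.95 on a reservoir mask at 10 L/min. From the endpoint: 93-94 on oxygen becomes 86-87 in air, read in order (93 to 86, 94 to 87).

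**Assumptions.** Baseline is the reference value, because the protocol names none. FiO2 in room air is 0.21. "SpO2 decrease > 5% in ambient air" is tried both as percentage points and as relative percent.

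**1. Can the printed pair be reproduced?** Not from Appendix 1. With Appendix 3 and PaO2/FiO2 held constant (a simplification), the FiO2 that maps one reading to the other is PaO2(on oxygen) × 0.21 / PaO2(in air):

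- 93 to 86: 69 × 0.21 / 52 = 0.279
- 94 to 87: 73 × 0.21 / 53 = 0.289
- crossing the pair: 69 × 0.21 / 53 = 0.273 and 73 × 0.21 / 52 = 0.295

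The pair therefore fits an FiO2 of about 0.27-0.30, close to 2 L/min by nasal cannula. On the same basis, 93-94% on oxygen corresponds to:

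| Nasal cannula flow | Ambient-equivalent PaO2 (mmHg) | SpO2 in air, about |
|---|---|---|
| 1 L/min | 60.4-63.9 | 90-92% |
| 2 L/min | 51.7-54.7 | 86-88% |
| 3 L/min | 45.3-47.9 | 81-83% |
| 4 L/min and above | below 44 | below 80% |

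The printed pair gives 86-87% at every flow.

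**2. Failure without a measured fall.** On Day 4 the patient is on 1 L/min that cannot be stopped.

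| Baseline in air | Day 4 on oxygen | Converted | Fall | Failure? |
|---|---|---|---|---|
| 93 | 93 | 86 | 7 points (7.5%) | yes |
| 93 | 94 | 87 | 6 points (6.5%) | yes |
| 92 | 93 | 86 | 6 points (6.5%) | yes |
| 92 | 94 | 87 | 5 points (5.4%) | only if relative |
| 91 | 93 | 86 | 5 points (5.5%) | only if relative |
| 90 | 93 | 86 | 4 points (4.4%) | no |

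PaO2/FiO2 on Day 4 is 69/0.24 = 288 at 93% and 73/0.24 = 304 at 94%. The protocol's hypoxemia grid calls these mild and normal.

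**3. Rise in oxygen need without failure.** Baseline is 93-94% at FiO2 0.24 and Day 4 is 93-94% at FiO2 0.60. Both convert to 86-87, a change of at most 1 point (1.2%), so there is no SpO2 failure. PaO2/FiO2 goes from 288-304 to 69/0.60 = 115 or 73/0.60 = 122, still above 100. With respiratory rate below 30 the composite is not a failure. PaO2/FiO2 reaches 100 only at FiO2 69/100 = 0.69 (SpO2 93%) or 73/100 = 0.73 (SpO2 94%).

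**The case against.** The strongest reply is that the conversion applies only when oxygen cannot be discontinued, and that a patient in room air at baseline who cannot come off oxygen on Day 4 may well have progressed. The first half stands. A reader might infer that starting low-flow oxygen is by itself a failure. The documents do not support that, because a patient who can be read in room air is not converted, and the false fall needs a room-air baseline of about 92-93% or more. The second half is a fair clinical view, but the endpoint does not define oxygen dependence as a failure. It defines a size of fall, and the conversion supplies that fall.

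It can also be said that the pair is only an example and that the full chart lies outside the protocol. That is true, but it leaves the rule for other readings undefined here.

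A reader might also infer that even extreme rises in oxygen need escape. They do not: 93% on a reservoir mask at 10 L/min gives 69/0.95 = 73 mmHg, which fails through PaO2/FiO2.

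Finally, a fall of more than 5% does not match the severe class in the secondary endpoint ("SpO2 status defined as"), which is ≤90%. That is not an error. A change criterion and an absolute class serve different purposes, and choosing between them is a matter of design.

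**Conclusion.** The point holds as a defect in the stated primary endpoint. The on-oxygen SpO2 rule cannot be followed from Appendix 1, and its only example misclassifies in both directions by the protocol's own Appendix 3. The failure without a measured fall needs three things together: a room-air baseline of about 92-93% or more, a Day 4 reading of 93-94%, and low-flow oxygen that cannot be stopped. The missed rise runs up to an FiO2 of about 0.69-0.73 at 93-94%, provided respiratory rate stays below 30.

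The size of the dilution cannot be derived. As illustration only, take the 0.40 and 0.10 of Section 11.4, which are death rates and not Day 4 failure rates, with 30 per arm, and let a share f of non-failures be misflagged in both arms. The observed rate becomes p + (1 − p)f. Exact Fisher power (two-sided 5%) is 70.5% at f = 0, 66% at 2%, 61% at 5%, 51% at 10% and 37% at 20%. At f = 20% the rates are 52% and 28%, so the difference is 24 points instead of 30. No value of f has a source in the document, and the study claims no formal power, so a stated loss of power should not be read into this point.

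**What to change.** Amend the primary endpoint wherever it appears:

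- Remove the NEWS-2 conversion. Apply the SpO2-fall criterion only when both readings are in ambient air. For a patient on oxygen at either time, judge oxygenation by the existing PaO2/FiO2 component, measured or from Appendix 3.
- Keep the >5% threshold, but name the reference value and say whether it means points or relative percent.
- List PaO2/FiO2 ≤100 as a separate component in Section 8.1.1 and in the Synopsis statistical text, as Section 11.5.1 already does.
- Reconcile Appendix 1 and inclusion criterion 5 with the text. Which conversion is clinically right is not judged here.

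**Cost.** Changes to the protocol, eCRF and SAP wording. SpO2 and PaO2/FiO2 are already scheduled on Day 4 (Section 7.7). The visit lists do not name device and flow, so confirm that the eCRF captures them wherever Appendix 3 is to be used. The SpO2 criterion will apply to fewer patients. Rises in oxygen need that stay above a PaO2/FiO2 of 100 will remain uncounted, as they are now; this change removes the false falls and the ambiguity, but not that gap.

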### List of Abbreviations and Definitions

| Abbreviation    | Definition                                                               |
|-----------------|--------------------------------------------------------------------------|
| ACM40           | All Cause Mortality at day 40                                            |
| ADA             | Anti-glenzocimab antibodies                                              |
| AE              | Adverse Event                                                            |
| ADR             | Adverse Drug Reaction                                                    |
| aPTT            | activated Partial Thromboplastin Time                                    |
| ARDS            | acute respiratory distress syndrome                                      |
| Cl t | Total Clearance                                                          |
| CONSORT         | Consolidated Standards of Reporting Trials                               |
| CRA             | Clinical Research Associate                                              |
| CRF/eCRF        | Case Report Form/ electronic Case Report Form                            |
| CRO             | Contract Research Organization                                           |
| cPRP            | concentrated platelet rich plasma                                        |
| GCP             | Good Clinical Practice                                                   |
| GFR             | Glomerular Filtration Rate                                               |
| DSMB            | Independent Data Safety Monitoring Board                                 |
| Fab             | Fragment of Monoclonal Antibody                                          |
| FIH             | First In Human                                                           |
| FIP             | First In Patient                                                         |
| GCP             | Good Clinical Practice                                                   |
| GPVI            | Platelet Glycoprotein VI                                                 |
| IEC/ IRB        | Independent Ethics Committee / Independent Review Board                  |
| IMP             | Investigational Medicinal Product                                        |
| INR             | International Normalized Ratio                                           |
| MED             | Minimum Effective Dose                                                   |
| MTD             | Maximum Tolerated Dose                                                   |
| NCI-CTCAE       | National Cancer Institute-Common Terminology Criteria for Adverse Events |
| NOAEL           | No Observed Adverse Effect Level                                         |
| PD              | PharmacoDynamics                                                         |
| PK              | PharmacoKinetics                                                         |
| PPS             | Per Protocol Set                                                         |
| PT              | Preferred Term                                                           |
| SAE             | Serious Adverse Event                                                    |
| SAP             | Statistical Analysis Plan                                                |
| SDV             | Source Data Verification                                                 |
| SmPC            | Summary of Product Characteristics                                       |
| SOC             | Standard Of Care                                                         |
| SS              | Safety Set                                                               |
| SUSAR           | Suspected Unexpected Serious Adverse Reaction                            |
| TCR             | Tissue Cross Reactivity                                                  |

|      |                                  |
|------|----------------------------------|
| TEAE | Treatment Emergent Adverse Event |
| WHO  | World Health Organization        |

## 1. INTRODUCTION AND BACKGROUND INFORMATION

### 1.1 COVID-19 Pandemic

Recent observations have demonstrated that as well as their hemostatic function, platelets contribute to tissue injury. In particular, studies during the past decade have implicated platelets in experimental lung injury and clinical Acute Respiratory Distress Syndrome (*for a review see Middleton EA. et al. AJRCMB 2018*). Indeed, platelets are recognized for their inflammatory role and as immune effector cells in the lungs. On the one hand, platelets are a reservoir of numerous soluble mediators that include pro-inflammatory cytokines and pro-fibrotic growth factors. On the other hand, platelets interact with leukocytes and endothelial cells.

The P-selectin/PSGL-1 axis has been extensively documented for its role in the interaction between platelets and polymorph nuclear cells (PMNs) and is also involved in platelet interactions with inflammatory endothelial cells.

Platelets amplify the formation by PMNs of neutrophil extracellular traps (NETs), the pathogenic role of which has been well established in so called thrombo-inflammatory processes. Platelets have complex interactions with endothelial cells which has consequences regarding endothelial permeability and vascular integrity.

The platelet count is altered in a context of critical illness, and thrombocytopenia is associated with a poor prognosis in ARDS, including H1N1 influenza infection (*Lopez-Delgado JC et al. Swiss Med Wkly 2013; 143:w13788*). Platelet-derived TLT-1, a marker of platelet activation, is also a poor prognostic indicator in ALI/ARDS (*Morales-Ortiz J. Blood 2018; 132:2495*). The inflamed lung is a site of platelet sequestration with fibrin thrombi in micro-vessels. Intravascular fibrin deposition and the formation of platelet-fibrin thrombi are key features of septic acute lung injury (ALI) in humans (*see review by Bozza FA et al. AJRCMB 2009; 40:123134*). The observation of low plasma fibrinogen levels together with elevated D-dimers that are associated with a poor prognosis in Covid-19-infected patients is in favor of a pathogenic accumulation of fibrin and platelets in their lungs, contributing to ALI and its evolution toward lung fibrosis.

In the particular case of viral infection, activated platelets and platelet-monocyte aggregates have been identified in blood samples from patients with ARDS caused by influenza A (*Rondina MT et al. Chest 2012;141:1490*). It has been proposed that activated platelets mediate aberrant hemostasis and maladaptive “hyper” inflammation by interacting with leukocytes and endothelial cells in the context of severe influenza infection (*Yang Y. et al. Cell Mol Immunol. 2016;13:432*). The infection of lung endothelial cells by viruses, resulting in platelet adhesion, is suggested to be a mechanism for influenza-induced ALI, based on parallel studies of human and mice lung microvascular endothelial cells and mice infected with H3N2 influenza A (*Katz JN et al. Chest 2011;138 :658; Sugiyama MG et al J Virol. 2016;90/1812*). In a mouse model of severe infection by influenza virus A, histopathologic studies demonstrated an accumulation of activated platelets in the lungs (*Lê VB et al. Am J Respir Crit Care Med 2015 ;191:804*). During the same study, viral proteins were detected within platelets.

Serotonin and Il-1 $\beta$  were found in bronchoalveolar lavage specimens, with serotonin being largely stored in platelets that released it following activation, while Il-1 $\beta$  was being produced by activated platelets. Genetic deficiency and pharmacological inhibitors of platelet activation diminished histologic markers of acute lung inflammation and mortality in infected animals. By contrast, the activation of protease-activated receptor 4, a key platelet receptor for thrombin in mice, worsened ALI and increased mortality, indicating that platelets contributed to lung damage in this model and suggesting that antiplatelet drugs might interrupt the course of inflammatory injury in influenza pneumonia. Observations during a second study indicated that H1N1 influenza activates platelets via a complex mechanism that includes the Fc $\gamma$ RIIA immunoreceptor and thrombin generation, thus involving both the innate and adaptive immune pathways (*Boilard E et al. Blood 2014; 123:2854*). Antiplatelet therapy may therefore offer a useful adjunctive strategy to fight virus-induced ALI. Most studies in human have focused on aspirin (ASA) yet but no definitive results have been obtained so far.

It should also be noted that platelets may contribute to iatrogenic complications, particularly when mechanical ventilation is excessive (*Matthay MA. et al. J Clin Invest 2012;122:2731; Yadav H et al. Am J Respir Crit Care Med 2017;195:725*).

More specifically, infection by SARS-Cov-2 is increasingly being recognized as causing both inflammatory and vascular injuries (*Wadman Science 2020*). Typically, severe pulmonary disease in SARS-Cov-2-infected patients is associated with uncontrolled inflammation and cytokine production ('cytokine storm') and displays the characteristics of ARDS. Indeed, an interim analysis of two clinical trials indicated that controlling the level of IL6 receptor activation can improve the prognosis in patients with severe Covid-19 respiratory distress (*in press*). As mentioned above, platelets have been shown to be important contributors in ARDS and the presence of platelet and fibrin thrombi in the lungs has been observed during the histological analysis of lungs from deceased patients (*Fox et al, MedRXiv pre-print, 2020*). Additionally, the huge quantities of growth factors released by activated platelets may favor the development of lung fibrosis as assessed from clinical and radiological signs and CT scans (*Xu VH, J infection 2020*).

Specifically, SARS-Cov-2 infects many cells and organs beyond the lung epithelium. In particular it enters blood cells. Endothelial cells have been shown to be infected by the virus, causing "endothelitis" (*Varga et al Lancet 2020*). Inflamed endothelial cells acquire an ability to trigger the adhesion of blood cells, including platelets. Furthermore, they lose their capacity to inhibit the coagulation cascade, allowing the generation of thrombin at the surface of activated platelets and fibrin formation that ultimately recruits more platelets. Microvascular and macrovascular thrombosis have been observed in several territories (such as the lung and skin micro-vessels, as well as in large cerebral arteries) in SARS-Cov-2-infected patients (*Tchachil J Thromb Haemost 2020, Chen J Lancet Infect dis 2020, Oxley TJ NJM 2020*). Biological findings highlight a prothrombotic state (including high plasma fibrinogen, FVIII, and platelet counts). Importantly, elevated D-dimers, the end product of fibrin degradation by fibrinolytic enzymes, are associated with an elevation of inflammation markers and have a poor prognosis in seriously affected Covid-

19 patients. In the most severe cases, signs of intravascular coagulation are shown, including platelet consumption and a prolonged prothrombin time (PT). As a consequence, the administration of low molecular weight heparin to prevent DIC has been recommended by several Learned Societies, including the ISTH. Importantly, sera from Covid-19 patients has been shown to contain elevated levels of cell-free DNA, myeloperoxidase (MPO)-DNA, and citrullinated histone H3 (Cit-H3); the latter two are highly specific markers of NETs. Cell-free DNA is strongly correlated with acute phase reactants and the neutrophil count. Cit-H3 correlates with platelet levels, thus favoring a role for platelets in the formation of NETs in this context (*Zhuo et al JCI insight 2020*).

One potential benefit of inhibiting platelet activation in SARS-Cov-2-infected patients has been suggested by two reports: the first was a proof-of-concept trial where dipyridamole, which inhibits platelet cAMP phosphodiesterase, improved clinical outcomes in patients with Covid-19 (*Liu X et al Acta Pharm Sin B 2020*); the second concerned the observation that the administration of Ibrutinib, a Bruton kinase inhibitor with a potent antiplatelet effect (*Rigg Am J Cell Physiol, 2016*) to a patient with a Waldenstrom disease and Covid-19 symptoms rapidly improved their oxygenation parameters (*Treon et al Blood 2020*).

To date, the use of more conventional antiplatelet agents in Covid-19 patients has not been reported. However, it should be noted that due to the aggravating effect of non-steroid anti-inflammatory drugs in Covid-19 infections, ASA at doses >100 mg/day may constitute a risk in this case. Furthermore, ASA has limited effects on activated platelets and in particular it is not a good inhibitor of the externalization of P-selectin and leukocyte-platelet interactions. Antiplatelet agents targeting the platelet ADP receptor P2Y12 or fibrinogen receptor (integrin  $\alpha$ IIb $\beta$ 3) involve too high a risk of bleeding for them to be administered in these patients.

